| \| 1) to determine whether a mobile phone-based 8-week behavioral program of a brief mindful interoceptive exposure task (MIET) is feasible and acceptable to patients with cLBP.  2) to determine whether MIET can increase below-average interoceptive awareness (as assessed by the MAIA) in patients with cLBP. We will offer the MIET to the participants in the cohort studies of the BACPAC REACH study (U19) living in the Bay Area, applicants of the Intensive Pain Rehabilitation Program at the VA, and other patients with cLBP, and validate it on self-report outcomes (pain intensity/ interference) *and* objectively (QST and fMRI**)**with 30 participants over 8 weeks, who fit a low interoceptive awareness phenotype.  3) To assess potential changes in chronic pain-related attitudes, believes and coping styles secondary to the intervention. In addition to psychological questionnaires, we will use qualitative exit interviews in 20 selected participants to explore phenomenological differences in patients' attention styles that may be associated with benefits for pain scores.  4) to assess whether potential changes in self-reported pain outcomes and/or objective QST measures are correlated with potential changes in interoceptive awareness (MAIA). All 30 participants will undergo pre-post assessment of pain intensity (NRS), pain interference (PROMIS-29), and QST.  5) to assess whether changes in self-reported interoceptive awareness (MAIA) are associated with changes in brain activity and connectivity. All 30 participants will undergo pre-post assessment of the MAIA and the fMRI Anticipation/Attention task. \| \| --- \| |
| --- | --- |

Design:

This is an uncontrolled, exploratory, mechanistic observational pilot study without control group for the validation of a behavioral task in individuals with chronic pain.

All subjects undergo:

1) questionnaire tests

2) psychophysical testing of cutaneous thermal sensitivity. Using previously validated procedures, we will examine each participant's sensitivity to temperature stimulation.

3) Functional Magnetic Resonance Imaging (fMRI) on the brain.

4) daily pain assessments by electronic momentary assessments (EMA) over 8 weeks

Background and Significance:

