**Phone/Zoom contacts (~10-30 minutes each for 7 calls)**:  Once a week after the initial training, the SRA will contact the participants by phone or zoom and go over any potential difficulties and barriers. If participants encounter difficulties or have questions, they are always able to leave a voice mail with the SRA for requesting a call back.

**Visit 3 (~ 1 hour)**: Two weeks after the initial training, participants will have another 1-hour zoom session with the PI to go over the experience of the last 2 weeks and discuss potential adjustments if needed.

**Visit 4 (2 to 4 hours)**: Eight weeks after the initial training session, participants will be scheduled for the follow-up QST and fMRI at the VA. Both QST and fMRI will be the same as in Visit 1. Communication from the SFVAMC will be done by phone and not include any video calls by Zoom.

**Repeat Questionnaires (~45-60 minutes)**: Participants will answer questionnaires online (Qualtrics) or on paper. Except demographics and social background questions, the questionnaires are the same as at baseline.

**Potential Visit 5 - Qualitative Interviewing (2 hours):** 20 of the participants will be invited for a follow-up 2-hour interview with [name] for (a) debriefing and (b) eliciting details about the phenomenology of the participants' attention style^3^ during the task performance of the past 8 weeks. The20 interviews will be in selected participants, 10 with strong (upper tercile) and 10 with weak (lower tercile) change scores in pain impact outcomes. This interview will be conducted in person if the COVID-19 situation allows, otherwise the interviews will use the Zoom platform.

^4^ Craig AD, Bushnell MC (1994) The thermal grill illusion: unmasking the burn of cold pain. Science 265:253-55. Available at <https://doi.org/10.1126/science.8023144>

^5^ Vierck Jr. CJ, Cannon RL, Fry G, Maixner W, Whitsel BL (1997) Characteristics of temporal summation of second pain sensations elicited by brief contact of glabrous skin by a preheated thermode. J Neurophysiology 78:992-1002

^6^ Nir R, Yarnitsky D (2015) Conditional pain modulation. Curr Opinions Suppot Palliat Care 9:131-7

Questionnaire Instruments:

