25) Pain Anxiety Symptoms Scale - Short Form (PASS-20) - (items 6-10, 16-20)*[McCracken et al. 2002]*(10)*

26) Five Facets Mindfulness Questionnaire (FFMQ) *[Baer et al. 2006]*(39)

27) CHILD TRAUMA QUESTIONAIRE (CTQ) – SHORT FORM [Bernstein et al.1995]

28) COLUMBIA-SUICIDE SEVERITY RATING SCALE (C-SSRS) [Posner et al. 2011]

Analyses:

**Overall Analysis Approach:**Preliminary analysis will be performed to confirm that key data variables are clean and complete. We will use sex and age as covariate, as insula function varies across sex and age. The principal analysis will use 'intent-to-treat' methods, in which all observations will be included for individuals, regardless of adherence to the protocol. As a secondary analytic method, we will also perform as-performed analyses with those who respond and enter data to at least 70% of phone prompts.

| **Table 1: Feasibility and acceptability assessment** | |
| --- | --- |
| **Feasibility Questions** | **Feasibility Measures (benchmark metrics)** |
| Can I recruit my target population? | Number screened (10 per month); number enrolled: (5 per month). *We will assess the number of enrolled participants from each outreach method, identify and address specific barriers to recruitment, modify emphasis on recruitment where needed, and use results to plan recruitment for subsequent studies.* |
| Can I keep participants in the study? | Retention rates for study measures (≥80% completion). *If target is not met, we will use feedback from participant interviews to modify retention steps.* |
| Are the assessments too burdensome? Can we complete outcome assessment? | Proportion of planned pre- and post-intervention assessments completed (≥80%), we will assess duration of assessments with quantitative and qualitative participant feedback. *If targets are not met, we will consider ways to shorten assessments.* |
| Is MIET acceptable to participants? | Acceptability ratings (≥8 on a 0-10 scale for ≥80% of participants); we will add qualitative participant assessments and document reasons for dropouts. *If target is not met, we will use feedback from participant interviews to modify intervention components* |
| Are phone based task and assessment of pain intensity/interference feasible? | Proportion of EMA assessments responded to (≥70%). Qualitative data on acceptability.*If target is not met, we will use feedback from participant interviews to modify EMA assessment procedures* |

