**Statistical Design and Power**: The primary purpose of this study is to determine feasibility and validate a novel mindfulness and interoceptive exposure-based intervention (MIET) in a subtype/phenotype of cLBP patients with low (below average) interoceptive awareness to determine initial clinical utility as a basis for future research. To achieve this, we will offer the MIET to the participants in the UCSF REACH Clinical Core cohort and the IPRP program at the SFVAMC, validate it on self-report outcomes (pain impact) *and*objectively (QST and fMRI Anticipation/Attention task à BBC proposal**)** with 30 participants over 8 weeks, who fit a low interoceptive awareness phenotype. Statistical power was estimated based on feasibility to find significant changes in disability outcomes (primary outcome, pain impact at 8 weeks.

In a very first pilot study of MIET in Australia participants experienced a significant reduction in pain intensity with a standardized effect size of *d*=1.37.1 This report may be overly optimistic. Assuming 10% attrition, we would be able to detect a ES *d*=0.78 (two-tailed; alpha 0.05, beta 0.2). For these preliminary estimations of the effect size, we used power calculations on the basis of the normal approximation with a 5% significance level for a 2- sided test, we determined that a sample size of 30 patients would provide adequate power (.70–.93) to detect minimal clinically important change. As this is a proof-of-concept study rather than an efficacy study, we will primarily assess for standardized effect sizes (Cohen’s *d*with 95% confidence intervals).

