*Single-subject Functional Analysis of Regional Activation Maps*: Average activation within each region will be subjected to regression analysis by way of LASSO. The LASSO regression model will be executed in R using the glmnet package for Lasso and Elastic-Net Regularized General Linear Models. LASSO will be performed on a single-subject basis to create subject specific models that best separate conditions of interest (e.g. high pain anticipation from low pain anticipation). Logistic regression methods such as LASSO allow for a smaller number of predictors to be included in the model, allowing the experimental pain task to be shortened and optimized. Regression will be then fit to the training set and will be optimized by cross-validating the model 100 times. This will allow for accurate and consistent discrimination between single-subject neurobiological patterns of different conditions. We can then apply these LASSO predictions on the test set (e.g., anticipation during uncertainty) at a probabilistic level, based on the correlation of the activation statistic to the cross-validated glmnet model. Thus, each participation can be labeled individually on the condition of interest.

**Qualitative Exit Interviews:**In-depth qualitative semi-structured interviews will be conducted after the final assessment. We will use the micro-phenomenology method by Petitmengin^3^ and probe the first-person experience in managing pain by either the narrative or the interoceptive awareness approach. This method has been developed to capture subjective processes in meditation and consciousness research (directed by Francisco Varela). It attempts to combine and mutually enlighten neural and experiential descriptions of cognitive processes and holds promise for providing additional heuristic information on the micro-phenomenology of interoceptive awareness and mind-body approaches in general. We will conduct 20 elicitation interviews in selected participants, 10 with strong (upper tercile) and 10 with weak (lower tercile) changes in pain impact outcomes.

References:

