Only designated study personnel included explicitly on the current IRB application will have access to any study records (both paper and electronic). No research results will be added to the patient's medical record unless medically necessary. Data will only be shared with those parties specified on the HIPAA form, which includes UCSF, UCSF IRB personnel, VA regulatory personnel, and the subject's primary care physician in the event of a medical complication.

Additionally, U.S.C 7332-protected sensitive information will be protected by the same rigorous standard as all other data. identifying information associated with this data will never be shared in reports or at conference proceedings, as with all other data.

Only designated study personnel included explicitly on the current IRB application will have access to any study records (both paper and electronic). No research results will be added to the patient's medical record unless medically necessary. Data will only be shared with those parties specified on the HIPAA form, which includes UCSF, UCSF IRB personnel, VA regulatory personnel, and the subject's primary care physician in the event of a medical complication.

Additionally, U.S.C. 7332-protected sensitive information will be protected by the same rigorous standard as all other data. Identifying information associated with this data will never be shared in reports or at conference proceedings, as with all other data.

VA research records will be retained within the VA-protected environment (e.g., VA server – please include the R Drive folder location/name, VA lab location, etc.), only accessible by authorized VA personnel, and disposed in accordance with the VHA Records Control Schedule (RCS 10-1). Any VA data shared with an external entity will be transmitted via FIPS 140-2-compliant encrypted methods as required per VA policy.

Financial considerations:

Subjects will be compensated for their time. Subjects will receive $100 per visit to the SFVAMC (2 visits = $200). They will receive $15 for travel reimbursement for each individual visit. Therefore, if a subject completes these 2 visits, they will receive up to $230 for SFVAMC visit compensation and travel compensation.

For the qualitative interview at the UCSF Osher Center, 20 of the 30 participants will receive $100 each and $15 for travel reimbursement.

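### Ten interviews from each outer tercile of 30 leave no room for attrition or refusal, and the protocol does not say how terciles are assigned while participants are still finishing

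*Protocol*

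**What the plan says.** Under Procedures, Potential Visit 5, the protocol invites 20 participants to a 2-hour interview and selects them as "10 with strong (upper tercile) and 10 with weak (lower tercile) change scores in pain impact outcomes". The interview is to debrief them and to draw out how they directed attention during the eight weeks of task practice behind them. The Qualitative Exit Interviews paragraph of the Analyses section repeats the rule as a commitment: "We will conduct 20 elicitation interviews in selected participants, 10 with strong (upper tercile) and 10 with weak (lower tercile) changes in pain impact outcomes". It places the interviews after the final assessment and gives no maximum interval.

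Financial considerations confirms the base: "20 of the 30 participants will receive $100 each". Specific Aims (aim 3) gives the same 20.

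Three other statements bear on whether this can be done:

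- Statistical Design and Power plans for loss: "Assuming 10% attrition".
- Table 1 sets a retention benchmark of at least 80%.
- Table 1 also sets an enrolment benchmark of 5 participants per month.

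The protocol states no replacement of dropouts, no reserve for refusals, and no rule for assigning terciles before all participants have finished.

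**The concern.** The interview count equals the whole of both outer terciles of the enrolled sample, so there is no slack. A participant without a post-intervention pain score has no change score and belongs to no tercile. An outer-tercile member who declines a further 2-hour visit cannot be replaced from within that tercile. To reach 20, staff would have to take people from the middle tercile and label them strong or weak changers.

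The second difficulty is timing. A tercile is defined relative to the whole sample, and participants finish at different times. Staff can wait until membership is settled, in which case early finishers describe fine-grained attention experience months after the practice ended. Or they can classify early, in which case some labels may later prove wrong. The protocol does not say which.

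At stake is aim 3, which uses these interviews to explore whether differences in attention style go with benefit in pain scores. The strong-versus-weak contrast carries that aim.

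**Working it through.** **Inputs.** 30 participants (Specific Aims; Financial considerations). 10 + 10 interviews (Potential Visit 5; Qualitative Exit Interviews). 10% attrition (Statistical Design and Power). At least 80% retention and 5 enrolled per month (Table 1). Post-assessment 8 weeks after training (Visit 4).

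**The plan's own figure.** Tercile size = n/3. With n = 30: 30/3 = 10 per tercile, and 2 × 10 = 20. The figure reproduces, but only with no losses and no refusals.

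**Effect of losses.** Tercile sizes under the usual quantile and rank-split conventions:

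| Participants with a change score | n/3 | Outer terciles | Maximum interviews |
|---|---|---|---|
| 30 | 10.00 | 10 and 10 | 20 |
| 29 | 9.67 | 10 and 10 possible (10/9/10) | 20 |
| 28 | 9.33 | 9 and 9, or 9 and 10 | 18 or 19 |
| 27 (10% attrition: 30 × 0.9) | 9.00 | 9 and 9 | 18 |
| 24 (80% retention: 30 × 0.8) | 8.00 | 8 and 8 | 16 |

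The rule therefore fails from the second loss.

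**How likely that is.** Assuming independent losses at 10%, P(no loss) = 0.9^30 = 4.2%. P(at most one loss) = 0.9^30 + 30 × 0.1 × 0.9^29 = 4.2% + 14.1% = 18.4% before rounding. At 20% the two figures are 0.1% and 1.1%.

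**Acceptance.** The protocol gives no acceptance rate. Even with all 30 completing, if each invited person accepts with an assumed probability of 90%, P(all 20 accept) = 0.9^20 = 12%. From 18 eligible people, the expected number of interviews is 18 × 0.9 = 16.2, or 18 × 0.8 = 14.4 at an assumed 80%.

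**Timing.** Follow-up is the same length for everyone, so the gap between first and last finisher equals the gap in enrolment.

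- Evenly spaced at 5 per month: 29/5 = 5.8 months.
- In monthly groups of five: 30/5 = 6 groups, so 5 months from the first group to the last.
- The mean wait until the last finisher is 5.8/2 = 2.9 months. Participant k waits (30 − k)/5 months, so participants 1 to 19 wait more than 2 months.
- At an assumed slower rate of 2.5 per month, the first-to-last gap is 29/2.5 = 11.6 months.

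**When membership becomes certain.** With 30 completers, a person is certainly in the top 10 once at least 20 others are known to rank below, so no one can be certain before 21 have finished. At 5 per month that is 20/5 = 4 months after the first finisher. With 29 known, one place at each end can still depend on the last score, so the full set of 20 is settled only then.

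**The case against.** **One loss does not break the rule.** A reader might infer that a single dropout makes 10 + 10 impossible. It does not: 29 completers can split 10/9/10.

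**Membership is not unknown for everyone until the end.** A reader might also infer that no one can be classified before the last participant finishes. A very extreme changer can be classified with certainty once 21 have finished. It is the complete set that has to wait.

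**A late interview is not stated.** The protocol's wording on timing reads naturally as each participant's own final assessment, and its reference to the practice just completed points the same way. Running terciles would be compatible with the text. The document therefore does not support saying that early participants will be interviewed months late. What stands is that it does not say how sample-relative terciles and prompt interviews are to be combined. The 5 per month is also a recruitment benchmark and not an accrual schedule.

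**Dropout is not the same as having no pain score.** The repeat questionnaires can be done online or on paper, and pain is recorded daily by phone, so someone who misses the on-site visit may still have a change score. The 80% is a pass mark and not an expected count. Both are fair. The 10% is nonetheless the protocol's own planning figure, and 27 appears to be the count its authors used: the stated detectable effect of 0.78 agrees with 0.777 from a two-sample calculation with 27 per group. Whether that calculation suits this design is a separate matter. If 30 were read as 30 completers, the attrition point would fall, but full acceptance would still be needed.

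**The harm is modest.** At 27 completers, filling to 10 + 10 takes one adjacent-rank person per side, in an exploratory qualitative sample. The interviews also serve debriefing and feedback. This is right and limits the weight of the point.

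**Conclusion.** The stated interview sample is one the design does not deliver on its own assumptions. At 10% attrition the outer terciles hold at most 18 people, two short of the 20 planned. At the 80% benchmark they hold at most 16. These are ceilings at full acceptance. They assume that those lost have no pain change score and are not replaced; the protocol states no replacement.

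The timing gap is a separate omission. The final outer terciles are complete about 5 to 6 months after the first participant finishes if the enrolment benchmark is met, and later if it is not, while the interview is about the eight weeks just past. The delay itself is an inference from staggered enrolment and not something the protocol announces.

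The consequence is confined to the qualitative aim. The primary feasibility outcome and the quantitative analyses are untouched. The point is worth correcting because the correction is cheap.

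**What to change.** Under Potential Visit 5 and Qualitative Exit Interviews, and for the matching 20 in Specific Aims (aim 3) and Financial considerations, plan up to 10 interviews from each outer tercile of participants with a pain change score, and up to 20 in total.

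Then add how and when participants are classified:

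- Name one pain-impact measure. The present wording refers to outcomes in the plural, and the protocol lists pain intensity (NRS), PROMIS-29 interference and the PEG scale.
- Set cut-offs in advance, either as pre-set change values or as provisional tercile cut-offs, and apply them as each participant finishes.
- Interview within a set window after the participant's own Visit 4.
- Report each interviewee's final tercile alongside the classification used for selection.

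The cost is wording in four places, possibly fewer than 20 interviews, and some provisional classifications that differ from the final terciles. Pre-set change values carry a further risk: one category could stay nearly empty if most participants improve or most do not. Terciles avoid that, so dropping them altogether is not required. Keeping a firm 10 + 10 would instead mean enrolling about 34 participants at 10% attrition (30/0.9 = 33.3) or 38 at 20% (30/0.8 = 37.5). That would still leave no allowance for refusals.

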Funding:

Funding is provided by NIH-NIAMS U19AR076737 (Overall PI: [name]; directors of Bio-Behavioral Core: [name] and [name]) under title: UCSF Core Center for Patient-centric Mechanistic Phenotyping in Chronic Low Back Pain (UCSF REACH)

Research Plan and Hypotheses:

This is an exploratory, mechanistic observational study with 30 patients undergoing 8-week pre-post assessment without a control group for proof-of-concept: can mindful interoceptive exposure possibly recover decreased interoceptive awareness AND dysfunctional central pain processing, thereby potentially reducing pain impact?

Hypotheses:

This is a proof-of-concept observational study without rigorous testing of hypotheses. Preliminary hypotheses are:

1) the new brief mindful interoceptive exposure task (MIET) is feasible and is acceptable to patients with chronic low back pain (cLBP) (Primary Outcome)

2) in cLBP patients with low interoceptive awareness (= below average scores on the Multidimensional Assessment of Interoceptive Awareness; MAIA), an 8-week mobile phone-based interoceptive exposure task can increase interoceptive awareness and recover dysfunctional central pain processing (assessed by quantitative sensory testing, QST; and fMRI connectivity) (Secondary Outcome)

3) exploratory hypothesis: Pain intensity (NRS) and pain interference (PROMIS-29) will improve from pre to post intervention.

4) exploratory hypothesis: Improvements in pain intensity and interference will be correlated with changes in MAIA scores, QST and fMRI connectivity.

Specific Aims:

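### The stated detectable effect of d = 0.78 does not follow from the single-arm pre-post design: 27 completers give 0.56 SD of change, a conservative error to be restated

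*Protocol*

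**What the plan says.** The Research Plan and Hypotheses section describes "30 patients undergoing 8-week pre-post assessment without a control group". The Design section agrees: "This is an uncontrolled, exploratory, mechanistic observational pilot study without control group". No second group is planned for the pain outcomes.

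Statistical Design and Power plans the study "with 30 participants over 8 weeks, who fit a low interoceptive awareness phenotype", ties the power estimate to pain impact at 8 weeks, and then states: "Assuming 10% attrition, we would be able to detect a ES *d*=0.78 (two-tailed; alpha 0.05, beta 0.2"). It names the normal approximation with a two-sided 5% test as the basis of its calculations. It adds that "a sample size of 30 patients would provide adequate power (.70–.93) to detect minimal clinically important change", without giving the size of that change or its SD. It closes by saying that the main output will be Cohen's d with a 95% confidence interval.

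The Sample Size Justification section calls the number sufficient for a proof-of-principle pilot and refers back to this text for power.

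**The concern.** A single group measured twice calls for a within-person test, in which the number of pairs and the SD of the change determine the detectable effect. The printed 0.78 is well above what 27 pairs give on that scale, and it agrees with a formula for two independent groups that this trial does not have.

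It is the only detectable effect that the Protocol states, and the sample size section relies on it. The study is meant to inform later research, so a planner could carry 0.78 forward as the sensitivity of a 30-person pre-post study. The undefined d also affects the planned reporting: a d in SDs of change and a d in single-timepoint SDs are different numbers for the same data.

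**Working it through.** **Inputs, all from Statistical Design and Power unless noted**
- Enrolled: 30. Attrition: 10%. Completers: 30 × 0.9 = 27.
- Two-sided alpha 0.05, power 0.80: z-values 1.960 + 0.842 = 2.802.
- Stated detectable effect: 0.78.
- Design: one group, pre and post (Research Plan and Hypotheses; Design).
- Lower retention case: the 80% benchmark in Table 1, 30 × 0.8 = 24.

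**Step 1. Attempt to reproduce 0.78**

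| Calculation | Normal approximation | t-test |
| --- | --- | --- |
| One group, 27 pairs | 2.802/√27 = 0.539 | 0.560 |
| One group, 30 pairs | 2.802/√30 = 0.511 | 0.529 |
| One group, 24 pairs | 2.802/√24 = 0.572 | 0.597 |
| Two groups, 27 each | 2.802 × √(2/27) = 0.762 | 0.777 |
| Two groups, 30 each | 2.802 × √(2/30) = 0.723 | 0.736 |
| 27 split 14/13 | 2.802 × √(1/14 + 1/13) = 1.079 | 1.123 |
| 30 split 15/15 | not run | 1.060 |
| Two groups, 27 each, one-sided | 0.677 | 0.686 |

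Only the two-sample t-test with 27 in each group rounds to 0.78. Its power at exactly 0.78 is 0.803. The normal approximation, which the section names, gives 0.78 in neither design.

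**Step 2. The figure for this design, in SDs of the change score**

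With 27 pairs the detectable d_z is 0.560, and 0.78/0.560 = 1.39, so the printed value is about 40% too large on this scale. At d_z = 0.78 the paired t-test with 27 pairs has power 0.974, and 15 pairs would already give 80%.

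**Step 3. If d is scaled by the single-timepoint SD**

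With equal SDs at both times and pre-post correlation r, the detectable d is 0.560 × √(2(1 − r)). The Protocol gives no r, so these values are assumptions:

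| r | Detectable d, 27 pairs |
| --- | --- |
| 0 | 0.560 × 1.414 = 0.79 |
| 0.03 | 0.560 × 1.393 = 0.78 |
| 0.3 | 0.560 × 1.183 = 0.66 |
| 0.5 | 0.560 × 1.000 = 0.56 |
| 0.7 | 0.560 × 0.775 = 0.43 |

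So 0.78 is right for this design only at r of about 0.03.

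**Step 4. Precision of the planned estimate**

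Large-sample SE of d_z at 0.56 with 27 pairs: √(1/27 + 0.56²/(2 × 27)) = √(0.0370 + 0.0058) = 0.207. The 95% half-width is 1.96 × 0.207 = 0.41, about 0.4.

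**The case against.** The case for leaving the sentence alone has real substance.

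- **The scale is open.** The Protocol writes only d. On the single-timepoint scale the gap between 0.78 and the right value runs from nothing at r = 0 to 80% at r = 0.7 (0.78/0.43 = 1.8). This stands: 0.56, the 40% and the power of 0.974 hold for SDs of change, or equivalently at r = 0.5. It does not rescue 0.78, which would need two scores from the same person 8 weeks apart to be almost unrelated, in people selected for pain on at least half the days over 6 months. The Protocol states no such assumption.
- **The source of 0.78 is inferred.** A reader might conclude that a two-group formula was used by mistake. The match is close, but it needs a t-test, and the section names the normal approximation, which gives 0.762 for two groups. The documents do not record the calculation.
- **The two power statements might seem to contradict each other.** For 27 pairs, power of 0.70 to 0.93 corresponds to d_z of 0.50 to 0.69, which does not include 0.78. But that range is attached to 30 patients and to a minimal important change of unstated size, and nothing says that this change equals 0.78. An input is missing, and no contradiction is shown.
- **The practical harm is small.** Feasibility and acceptability are the primary outcome in the hypotheses, and pain improvement is exploratory there, although the power section calls pain impact primary. The benchmarks in Table 1 are all feasibility measures, and no success rule uses 0.78. A reader might infer that true effects between 0.56 and 0.78 would be dismissed as undetectable. The text does not say so, and the estimates are to be reported with intervals whatever their size.

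**Conclusion.** The stated detectable effect is wrong for the design as written. With 27 completers, a two-sided 5% paired t-test and 80% power, the figure is 0.56 SD of the change score (0.54 by the normal approximation; 0.60 with 24 completers). On the single-timepoint scale it depends on a correlation that the Protocol does not give, and it reaches 0.78 only when that correlation is close to zero.

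A reader might infer that the trial is too small. The opposite holds: at any appreciable positive correlation the design detects a smaller effect than claimed, so the error is conservative and does not undermine the sample of 30. This is a minor correction of a printed figure. The arithmetic is firm; the explanation of where 0.78 came from is only likely.

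**What to change.** Replace the sentence that gives 0.78 with wording such as: *With 27 completers a paired two-sided 5% t-test has 80% power for a within-person change of 0.56 SD of the change score (0.60 with 24 completers); the 95% CI for d has a half-width of about 0.4.*

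State which SD standardizes d, both here and for the reported effect sizes. If it is the single-timepoint SD, give the assumed pre-post correlation and the matching detectable d from the table above. Make the named method agree with the figure: t-test for 0.56, normal approximation for 0.54.

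If the power range of .70 to .93 is kept, add the minimal important change and the SD behind it, or point to where they are given.

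The cost is a few sentences of wording. Sample size, assessments and conduct are unchanged.
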